#### Outcomes

2.1.4

The primary outcome of the evaluation is the caregivers' self‐efficacy expectations (see Section 1.1). Secondary outcomes (see Section 1.2) include health literacy, perceived stress, health‐related quality of life, empowerment and caregiver burden. All questionnaires used for the assessment are available in German and Turkish (as well as English) and have been validated by previous research (see Section 2.3.3).

#### Participant Timeline

2.1.5

The Diversity‐On project is scheduled to run for a period of 36 months, starting in January 2023 and ending in December 2025. The intervention will be developed during the first year of the project. Recruitment of study participants will begin at the end of 2024. An overview of the timeline is given in Figure 1.

**FIGURE 1 jan16443-fig-0001:**
[figure not shown]
Time schedule of enrolment, interventions and assessments following the recommended SPIRIT template (Chan et al. 2013).

#### Sample Size

2.1.6

Given a power of 80%, an alpha error of 5% and a standard deviation of 4 in the primary outcome measure and an estimated intraclass coefficient of 0.15, a sample size of a total of 26 clusters, each consisting of 5–6 caregivers, makes it feasible to identify mean differences of 2.5 on the SWE scale. This constitutes a medium effect size (Cohen's *d* = 0.6). The primary and secondary hypotheses will be assessed through multivariate testing using structural equation modelling.

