#### Interventions

2.1.3

The ‘Diversity‐On’ intervention consists of an online self‐help platform that promotes diversity, encourages participation and caters to the diversity of the participants. This self‐help platform will facilitate a guided group specifically for caregivers of individuals living with dementia, utilising the previously mentioned storytelling methodology. The platform will be implemented for people with a Turkish migration background.

In total, 130 family caregivers will be allocated to 26 online support groups of about 5–6 persons each, comprising both intervention and control (as described below). The 26 groups will be randomised into an intervention and a control group, each comprising 13 groups.

[Intervention]: The individuals randomly assigned to the intervention group are divided into 6 groups of approximately 6 individuals, with each group representing specific diversity characteristics. In the intervention group, online self‐help sessions will be delivered using the previously mentioned diversity‐sensitive storytelling approach. The 6 intervention groups will convene on a monthly basis to discuss one story at each meeting. All participating co‐researchers of the intervention groups will receive prior training on the utilisation and management of the stories, as well as on the conduct of an online support group (opening, story presentation, discussion facilitation and closing).

[Control]: The individuals randomly assigned to the control group will also be randomly divided into 6 groups, comprising approximately 6 individuals each. The 6 control groups will convene on a monthly basis to conduct conventional support group sessions that are not storytelling‐based and that are not specifically tailored to the participants' diversity sensitivity.

The self‐help groups will be managed by members of the council of family caregivers. In order to ensure the ethical integrity of the study, all meetings of both the intervention groups and the control groups will be attended by one member of the project team.

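### The trial is sized for one clustered mean difference on the SWE, but the primary hypothesis is assigned to multivariate structural equation modelling, whose usual large-sample tests exceed 5% with 26 groups

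*Protocol article*

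**What the plan says.** Section 2.1.6 (Sample Size) of the protocol article takes 80% power, a 5% alpha, "a standard deviation of 4 in the primary outcome measure" and, for the clustering, "an estimated intraclass coefficient of 0.15". From these it derives "a sample size of a total of 26 clusters, each consisting of 5–6 caregivers", as enough to detect a 2.5-unit difference in mean SWE. Section 2.1.3 (Interventions) gives the allocation: "The 26 groups will be randomised into an intervention and a control group, each comprising 13 groups".

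Sections 1.1, 2.1.4 and 2.3.3.1 name one primary hypothesis and one primary outcome, self-efficacy on the SWE, with five secondary outcomes. Section 2.3.3.1 describes the design as cluster-randomised with 2 × 13 groups.

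The only sentence on the quantitative analysis closes Section 2.1.6: "The primary and secondary hypotheses will be assessed through multivariate testing using structural equation modelling".

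**The concern.** The sample size rests on a univariate comparison of two means with a cluster design effect. The analysis sentence puts the primary and all secondary hypotheses under one multivariate method. It does not say which test carries the primary claim.

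SEM inference normally refers its statistics to a z or chi-square distribution. That is justified when there are many independent units. In this design the independent units for the arm comparison are the support groups, 13 per arm, so these reference distributions are too narrow.

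What is at stake is the primary p-value and confidence interval. The test may reject more often than 5% under no effect, and the stated 80% power belongs to a different analysis.

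**Working it through.** **Inputs from the article.** Difference 2.5, SD 4, intraclass coefficient (ICC) 0.15, 26 groups (13 per arm), N = 130, hence 130/26 = 5 per group. Alpha 5% is taken as two-sided, because only that reproduces 80%.

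**1. The plan's own figure.**
- Unclustered n per arm = 2 × [4 × (1.960 + 0.842)/2.5]² = 40.2, rounded up to 41.
- Design effect = 1 + (5 − 1) × 0.15 = 1.6.
- 40.2 × 1.6 = 64.3 per arm. 64.3/5 = 12.9, so 13 groups per arm, 26 in all, N = 130.
- Effective n per arm = 65/1.6 = 40.6. Standard error = 4 × √(2/40.6) = 0.888. 2.5/0.888 = 2.817.
- Power by the normal approximation = Φ(2.817 − 1.960) = 80.4%.

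The stated sample size is therefore correct for one clustered mean difference judged by a z test.

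**2. Power with a test that respects 26 groups.** Using t on 26 − 2 = 24 degrees of freedom and noncentrality 2.817, power is 77.1%. With 5.5 or 6 people per group it would be 79.1% or 80.8%.

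**3. True type I error of a nominal 5% test, 26 groups of 5, ICC 0.15.**

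| How the test might be run | Calculation | Type I error |
|---|---|---|
| SWE alone, clustering ignored | 2 × [1 − Φ(1.96/√1.6)] | 12.1% |
| SWE alone, cluster-robust SE without correction, z | P(\|t₂₄\| > 1.96 × √(24/26)) | 7.2% |
| SWE alone, two-level maximum likelihood (ML), z | simulation | 7.1% |
| SWE alone, random intercept by REML, z | simulation | 6.1% |
| Six outcomes jointly, Wald chi-square on 6 df | P(F₆,₁₉ > 12.59 × (24/26) × 19/144) = P(F₆,₁₉ > 1.53) | 22.1% |
| Six outcomes jointly, likelihood ratio on 6 df | P(F₆,₁₉ > 24 × (e^(12.59/26) − 1) × 19/144) = P(F₆,₁₉ > 1.97) | 12.0% |
| SWE alone, random intercept by REML, t on 24 df | simulation | 5.0% |

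The simulations used 100,000 balanced normal trials per scenario. The two-level ML figure varies little with the ICC: 6.0% at 0.05 and 7.1% at 0.30.

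**4. Effect of baseline adjustment, if a baseline SWE exists.** The baseline–follow-up correlation r is not in the article. Assume it acts equally at person and group level, so that the variance is multiplied by (1 − r²) and the noncentrality becomes 2.817/√(1 − r²). On 24 df, power is 80.8% at r = 0.3, 83.9% at 0.4, 87.7% at 0.5 and 92.2% at 0.6.

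**The case against.** The best defence is that the sentence says very little. It does not commit to one joint model, an omnibus test, item-level measurement models or a single-level analysis. Estimator, clustering term and degrees of freedom are commonly left to a full protocol or analysis plan, neither of which is shown. An SEM also yields an arm-to-SWE coefficient with its own test. With observed outcomes and a saturated structure, that coefficient is the mean difference the trial was sized for.

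Most of this stands, and it rules out three stronger readings that a reader might infer.

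- **That clustering will be ignored, or that an omnibus test will decide the primary claim.** The article states neither. It builds an ICC into the sample size and calls the design cluster-randomised. The 12% and 12–22% figures are therefore conditional.
- **That the model is too large to fit or will not converge.** This would need a specific model, such as one factor over all 47 health literacy items, which the article does not describe.
- **That SEM is wrong and a mixed model is right in itself.** A two-level ML SEM of the SWE alone is the same model as an ML mixed model and has the same 7.1% error with a z test. REML with a z test still gives 6.1%. The small-sample reference distribution is what restores 5%.

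The defence does not remove the published commitment. The article assigns the primary hypothesis to a stated method that differs from the powered comparison. Every usual large-sample form of that method examined here exceeds 5% with 26 groups.

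**Conclusion.** The point holds in a limited form. The powered comparison and the stated primary analysis do not match. The usual large-sample SEM tests are liberal with 26 groups: modestly so (about 6–7%) in the favourable case of a cluster-aware test of the SWE alone, about 12% if clustering is ignored, and about 12–22% if six outcomes were tested together. Which applies cannot be read from the article.

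These figures assume 26 balanced groups of 5, normal outcomes and an ICC of 0.15. Section 2.1.3 also speaks of six groups per arm. That is a separate inconsistency and is not used here, although the final number of groups sets the degrees of freedom.

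This should be fixed before analysis. It does not invalidate the design.

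**What to change.** Replace the last sentence of Section 2.1.6 with wording such as:

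*The primary analysis is the effect of arm on end-of-intervention SWE, estimated from a linear mixed model with a random intercept for support group, fitted by restricted maximum likelihood with Kenward-Roger or Satterthwaite degrees of freedom, and reported with a 95% confidence interval. This is the only primary test, at two-sided 5%. The same model is used for each secondary outcome. Structural equation modelling is supportive or exploratory.*

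A t test on group means with about 24 degrees of freedom would be an acceptable equivalent.

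No new data are needed, only wording. The cost is that power for 2.5 units at 5 per group becomes about 77%, which should be stated openly. If the SWE is measured at baseline (the schedule in Figure 1 is not shown), add it as a covariate. At assumed correlations of 0.3–0.6 this brings power to about 81–92%. It is an optional gain in precision, equally available within SEM, and is not what controls the error rate.

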#### Recruitment

2.1.7

##### Family Caregiver Recruitments for the Council

2.1.7.1

Recruiting family caregivers for the participatory council will be conducted together with voluntary welfare organisations and the project partners. Participation in the council is voluntary and requires informed consent. Participants in the council will receive written information about the study, the data protection concept and the declaration of consent in German and Turkish in advance. They will be given the opportunity to ask questions about the study before giving their written consent to participation.

##### Participant Recruitments for the Online Self‐Help Groups

2.1.7.2

130 family caregivers are expected to take part in the evaluation (see Section 2.1.6). Assuming a dropout rate of about 17%, 156 family caregivers of people living with dementia will be recruited for the self‐help groups by means of various cooperation partners, including welfare and self‐help organisations and family doctors working in districts with a high proportion of migrants, as well as through social media (e.g., Facebook and Instagram). Participation in the self‐help groups, as well as participation in the council will be voluntary and will take place after written information has been provided and informed consent has been obtained.

### Assignment of Interventions

2.2

#### Allocation

2.2.1

130 family caregivers will be allocated to 26 online support groups of about 5–6 persons each (see Section 2.1.3). The 26 groups will then be randomised into an intervention and a control group, each comprising 13 groups.

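### The protocol gives 130 both as the number allocated to the groups and as the number left after 17% dropout; if 130 are allocated and 17% are then lost, power is about 76%, not 80%

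*Protocol article*

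**What the plan says.** Section 2.1.6 (Sample Size) sets out the calculation: "Given a power of 80%, an alpha error of 5% and a standard deviation of 4 in the primary outcome measure", with "an estimated intraclass coefficient of 0.15". It concludes that 26 clusters of 5 to 6 caregivers suffice to detect "mean differences of 2.5 on the SWE scale".

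Section 2.1.7.2 (Participant Recruitments for the Online Self-Help Groups) expects 130 caregivers in the evaluation, refers back to 2.1.6, and continues: "Assuming a dropout rate of about 17%, 156 family caregivers of people living with dementia will be recruited" for the self-help groups. Here 130 is the number net of dropout.

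Section 2.2.1 (Allocation) reads: "130 family caregivers will be allocated to 26 online support groups of about" 5 to 6 persons, with 13 groups then randomised to each arm. Section 2.1.3 (Interventions) gives the same 130, 26 and 13, but goes on to describe each arm as 6 groups of about 6 people. In both sections 130 is the number placed in groups before any session takes place.

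**The concern.** The number allocated and the number analysed cannot both be 130 if 17% are lost in between. Sections 2.1.3 and 2.2.1 are the text that staff would follow when forming groups. Taken literally, they remove the dropout allowance that 2.1.7.2 builds in, and they do not say what happens to the other 156 − 130 = 26 recruits. The article does not say whether the 17% is lost before or after allocation. At stake is whether the primary comparison on the SWE scale has the power that 2.1.6 claims for it.

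**Working it through.** **Inputs from the article.** SD 4, difference 2.5, ICC 0.15, alpha 5% and power 80% (2.1.6); 13 groups per arm (2.1.3, 2.2.1); dropout about 17%, 156 recruited, 130 evaluated (2.1.7.2).

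**Assumptions.** Alpha is two-sided (the article does not say), group sizes are equal, dropout is spread evenly with no whole group lost, and there is no baseline adjustment.

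**1. The plan's own figure.**
- Unclustered n per arm = 2 × (1.96 + 0.8416)² × 4² / 2.5² = 40.2.
- Design effect with 5 per group = 1 + (5 − 1) × 0.15 = 1.60.
- 40.2 × 1.60 = 64.3 per arm; 64.3 / 5 = 12.86, rounded up to 13 groups per arm. This gives 26 groups and 130 people.
- Power with 65 per arm: SE = 4 × √(2 × 1.60 / 65) = 0.888; 2.5 / 0.888 = 2.817; Φ(2.817 − 1.960) = 80.4%.

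The stated 80% reproduces, with 130 as the number *evaluable*.

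**2. What the group sizes imply.** 26 × 5 = 130 and 26 × 6 = 156. The range of 5 to 6 per group therefore fits 156 at the start and 130 at the end. Also 156 × 0.83 = 129.5, so the 156 in 2.1.7.2 is the number needed before dropout.

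**3. 130 allocated, 17% then lost.**
- 130 × 0.83 = 107.9 evaluable; 107.9 / 26 = 4.15 per group; 53.95 per arm.
- Design effect = 1 + 3.15 × 0.15 = 1.47.
- SE = 4 × √(2 × 1.4725 / 53.95) = 0.935; 2.5 / 0.935 = 2.675; Φ(2.675 − 1.960) = 76.3%.

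**4. 156 allocated, 17% then lost.**
- 129.5 evaluable; 4.98 per group; design effect 1.597.
- SE = 0.888; 2.5 / 0.888 = 2.814; power 80.3%.

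**5. Margin.** With 13 groups per arm, 80% power on this formula needs m per group such that 40.186 × (0.85 + 0.15m) = 13m. This gives m = 4.90, or about 127.4 people in total. Losing 3 of 130 already takes power just below 80%.

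**6. Sensitivity to the reference distribution.** A cluster-level t test on 26 − 2 = 24 degrees of freedom, with the same standard errors and a noncentral t distribution, gives the last column.

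| Allocated, then evaluable | Normal approximation | t, 24 df |
|---|---|---|
| 130 evaluable | 80.4% | 77.1% |
| 130 allocated, 107.9 evaluable | 76.3% | 72.8% |
| 156 allocated, 129.5 evaluable | 80.3% | 77.0% |

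**7. Sensitivity to baseline adjustment.** Suppose baseline SWE is adjusted for and each SE shrinks by √(1 − r²). At an assumed correlation of r = 0.5, which the article does not give, the t-based power is 87.7% with 130 evaluable and 84.2% with 107.9. The t-based figure for 107.9 evaluable thus runs from 72.8% at r = 0 to 84.2% at r = 0.5.

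**The case against.** The strongest reply is that dropout is planned for and only the label on 130 is loose. Section 2.1.7.2 intends 156 recruits so that 130 are evaluated, and reaching 108 means taking 17% off a number that section already treats as net. If the 17% is lost between recruitment and allocation, allocating 130 is consistent. It is true that the shortfall is conditional. But the article does not state that reading. The 156 are recruited for the self-help groups themselves, and participants may withdraw at any time (2.4.4). On that reading, too, monthly sessions would start with no allowance for later loss, and the margin is under 3 people.

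A reader might go further and infer that the 80% is itself wrong and should be 77% even with 130 completers. The documents do not support that. The standard design-effect formula gives 80.4% and rounds up to the stated 13 groups per arm. The 77% arises only from a 24-df t test that the article does not name; 2.1.6 plans structural equation modelling. It is a fair small-sample caution, not an arithmetic error, and baseline adjustment could more than offset it.

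A reader might also infer that 26 consenting caregivers will be turned away. No text says so: 26 groups of 6 hold 156 people, and groups of about 5 to 6 are compatible with either total.

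**Conclusion.** The inconsistency is real: sections 2.1.3 and 2.2.1 use as the allocated number what 2.1.7.2 defines as the number left after dropout. If 130 are allocated and 17% are then lost, about 108 remain. Power falls by about 4 percentage points on the plan's own formula (80.4% to 76.3%), or to about 73% with 24 df. The result rests on dropout occurring after allocation and on the assumptions listed with the inputs. Allocating 156 restores about 80%. The correction should be made because the affected sentences are the operational ones and the loss is avoidable, though modest.

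**What to change.** In 2.1.3 and 2.2.1, state that 156 caregivers are allocated to 26 groups of about 6, to leave about 130 (5 per group) for evaluation. In the same edit, reconcile the 6 groups per arm in 2.1.3 with the 13 per arm stated there and in 2.2.1 and 2.3.3.1: 2 × 6 groups of about 6 hold about 72 people, which is neither 130 nor 156. Changing the 130 alone would leave that section contradicting itself.

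As a secondary point, note in 2.1.6 that the 80% is a normal-approximation figure and that on 24 df it is about 77% without baseline adjustment.

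The cost is wording only. Recruitment of 156 is already planned, and the number of groups in the sample-size calculation does not change.

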#### Implementation

2.2.2

The allocation sequence will be generated at random. The project team is responsible for enrolling participants and assigning them to either the intervention group or the control group. Subsequently, participants in both the intervention and control groups are allocated to small groups comprising 5–6 individuals. In the intervention group, the allocation will be made by the project team on the basis of the diversity characteristics of the participants. In the control group, the allocation process is randomised, with diversity characteristics not being taken into account.

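### The team that enrols caregivers also assigns them to arms, with no separation of roles or point of disclosure stated, and the order of grouping and randomisation is contradictory

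*Protocol article*

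**What the plan says.** Section 2.2.2 (Implementation) opens with "The allocation sequence will be generated at random" and continues: "The project team is responsible for enrolling participants and assigning them to either the intervention group or the control group". It then describes a second step: "Subsequently, participants in both the intervention and control groups are allocated to small groups". That step differs by arm. For the intervention arm, "the allocation will be made by the project team on the basis of the diversity characteristics of the participants". For the control arm: "In the control group, the allocation process is randomised, with diversity characteristics not being taken into account".

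Section 2.2.1 (Allocation) gives another order. Caregivers are first placed in 26 small groups, and then: "The 26 groups will then be randomised into an intervention and a control group, each comprising 13 groups".

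Section 2.1.3 (Interventions) contains both versions. Its opening paragraph on allocation randomises 26 groups, 13 to each arm. Its descriptions of the two arms speak of individuals who were randomly assigned and then divided into 6 groups per arm. It adds that every meeting in both arms "will be attended by one member of the project team". Section 2.3.3.1 calls the design cluster-randomised.

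**The concern.** Random generation of a sequence and protection of that sequence are two separate safeguards. The first makes the order of arms unpredictable in principle. The second stops the people who decide whom to approach, and when to enrol them, from knowing which arm comes next. Section 2.2.2 provides the first. It then gives enrolment and assignment to one unit without stating anything that provides the second.

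The unit concerned has the knowledge needed to select. It must know each caregiver's diversity profile to compose the intervention groups, and it develops the stories from an analysis done with the council. Recruitment under section 2.1.7.2 runs through partner organisations, family doctors and social media, which leaves discretion over whom to enrol and when.

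If enrolment were influenced by knowledge of the arm, the arms could differ in self-efficacy, motivation or burden before the first meeting. The primary outcome is a self-report questionnaire, completed by people who attend visibly different sessions. An initial difference that persisted would enter the estimated effect, and analysis cannot reliably remove selection at enrolment.

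**Working it through.** **Step 1: the possible orders, side by side.**

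| | Individuals first (2.2.2; arm descriptions in 2.1.3) | Groups first (2.2.1; allocation paragraph in 2.1.3) |
|---|---|---|
| Unit randomised | individual | small group |
| Order | arm, then small group | small group, then arm |
| Groups per arm | 6 in 2.1.3; no number in 2.2.2 | 13 |
| Diversity sorting in one arm only | possible, because the arm is known | not possible unless the arm is already known |

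*Individuals first.* Sorting follows assignment, so it cannot change who is in which arm. Attendance at meetings comes later still and cannot either. The exposure is at enrolment: a recruiter who can see the sequence can know the next arm.

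*Groups first.* If all groups were complete and randomised together, there would be no next arm to anticipate during enrolment. But section 2.2.2 requires groups sorted by diversity in one arm and formed at random in the other. Groups that exist before randomisation can differ in this way only if those forming them already know the arm. Sections 2.2.1 and 2.2.2 therefore cannot both be carried out as written without foreknowledge.

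**Step 2: reproduce the plan's own sample size (section 2.1.6).** Inputs: difference 2.5, SD 4, alpha 5% (two-sided assumed), power 80%, ICC 0.15, groups of 5.

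- Per arm without clustering: 2 × [4 × (1.960 + 0.842) / 2.5]² = 40.19.
- Design effect: 1 + (5 − 1) × 0.15 = 1.60.
- Per arm with clustering: 40.19 × 1.60 = 64.3, and 64.3 / 5 = 12.9, so 13 groups.
- Total: 26 groups and 26 × 5 = 130 caregivers, as stated. Who enrols or assigns does not affect this figure.

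**Step 3: what an imbalance would do, if there were one.** The article gives no figure for imbalance, so 0.5 and 1.0 units are assumed. Each is taken to persist fully to follow-up, with no true effect and no baseline adjustment.

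- Standard error of the difference: 4 × √(2 × 1.60 / (13 × 5)) = 4 × √0.04923 = 0.8875.
- Test: t with 2 × 13 − 2 = 24 degrees of freedom, critical value 2.064. The rejection rate comes from the noncentral t with noncentrality equal to imbalance / 0.8875.

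| Assumed imbalance | Share of the 2.5-unit target | Noncentrality | False-positive rate |
|---|---|---|---|
| 0 | 0% | 0 | 5.0% |
| 0.5 | 20% | 0.563 | 8.4% |
| 1.0 | 40% | 1.127 | 19.1% |

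**The case against.** The strongest reply is that this is silence in a condensed article. Who holds the sequence, and when it is disclosed, is often left to the full protocol. The project team is a collective, so one member may recruit while another holds the list. The article does not say that allocation is open or predictable, and staff who only carry out a concealed random sequence cannot steer anyone.

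Much of this stands. Bias is not demonstrated, concealment may be described elsewhere, and a division of labour would be compatible with the present wording. A reader might infer that the team can direct well-suited caregivers into the intervention arm, or that sorting the groups and attending meetings bias the comparison. The article does not support either inference. Assignment is described as random, and in the order of section 2.2.2 sorting and attendance come after the arm is fixed. Diversity-based grouping is also part of the intervention itself.

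The reply does not remove the whole point. Section 2.2.2 makes a positive statement that places both tasks with the same unit. A plan to generate the sequence at random does not answer the question of foreknowledge. The contradiction over the order of steps is in the text, whatever the full protocol adds.

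The objection to the percentages is also fair. The imbalances are chosen, and baseline adjustment, which the article neither states nor excludes, would reduce their effect.

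**Conclusion.** The point holds in limited form. As written, section 2.2.2 does not protect the randomised comparison from foreknowledge at enrolment, because enrolment and arm assignment sit with one team and neither a separation of roles nor a point of disclosure is stated. Selection bias is a risk, not a finding, and its likely size is unknown. The rates of 8.4% and 19% show only that modest imbalances would matter in a trial of this size. They rest on the assumptions in Step 3 and do not predict what will happen.

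The firmer part is the contradiction. Section 2.2.1 randomises groups already formed, section 2.2.2 assigns individuals and then groups them, and section 2.1.3 does both. Until this is settled, the article does not fix the point at which foreknowledge could act. One combination, groups formed first and sorted by diversity in one arm only, would require it. The point merits correction but does not invalidate the design.

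**What to change.** First reconcile sections 2.1.3, 2.2.1 and 2.2.2 on the unit randomised, the order of steps and the number of groups per arm.

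Then add to section 2.2.2 that the sequence is generated and held by an existing project member or partner who neither recruits nor forms groups, and that the arm is disclosed only after written consent and the baseline questionnaire are complete. The remaining wording depends on the unit:

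- If individuals are randomised, diversity sorting in the intervention arm follows disclosure.
- If whole groups are randomised, all 26 rosters are formed by one common rule, locked, and randomised in a single run. Sorting by diversity in one arm only is then not possible, so the description of the arms would have to change to match.

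If caregivers have already been enrolled, report who held the sequence and when arms were disclosed.

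The cost is a division of tasks among existing staff, a few sentences, and a short wait between enrolment and disclosure. The sample size is unaffected if the plan remains 26 groups.
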